### Aim

The primary aim of this research study is to compare the effect of 3 20-minute hand massage administrations by a trained nurse within 24 hours after cardiac surgery versus hand-holding (ie, simple touch) and standard care on the postoperative pain intensity of adult ICU patients.

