### Sample Size and Sampling Procedure

A power analysis was conducted using the G*Power 3 program [38] to estimate the sample size required to capture the potential effects of massage to decrease the primary outcome (pain intensity) and to strengthen the statistical conclusion validity. The mean treatment difference was observed to be greater than 1.5 in several RCTs [11,26,39,40] and approximates the clinically significant difference of 2 points on the 0 to 10 Numeric Rating Scale (NRS) [41]. This trial is powered to be able to detect a difference in the pain intensity score of 1.5 between the hand massage and standard care group. The standard deviation of pain intensity scores is approximately a 2.0 value, which was selected for the sample size calculation. To detect a mean difference in pain intensity scores of 1.5 points (SD 2.0) immediately after the third massage with a 2-sided significance level of .05 and power of .80 with equal allocation to 3 arms and a repeated measures between factors context with 3 measurements would require a minimum of 72 patients.

Given the low attrition rates observed with this patient population (0% [9,10,30] and 35/287 (12.2%) [29]), a 10% drop-out rate is considered in the calculation of the total sample size. Therefore, the final size required for this RCT is 79, and it will be reached using convenience sampling.

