### Outcomes

#### Primary Outcome

Pain intensity is the primary outcome and will be captured using the 0 to 10 NRS score. The analysis metric will be the change in pain intensity from baseline (preintervention) to immediately after each intervention and 30 minutes later.

Hand massage routine protocol.1. Hygiene: Wash hands with warm water.2. Hold/connect/breathe: Make initial contact with patient, embrace hand, take a deep breath, and place feet on floor.3. Apply cream to entire hand, dorsal and palmer aspects, including phalanges.4. Spread (5 times) dorsal aspect of hand, using thumbs like opening a book. Repeat 5 times on palmer aspect, using the other 4 fingers to grip and glide. Spread again 5 times dorsal aspect of hand and 5 times palmer aspect.5. Gently shake bottom hand; vibration will help the patient relax and let go of any tension.6. Rotate wrists 3 times in each direction. Hold wrist with one hand while the other holds the patient’s hand and facilitates the passive rotation.7. Stretch the carpal ridge 3 times along wrist crease.8. Caterpillar walk on the dorsal aspect of the hand, between the bones (ie, zoning).9. Pinch (dorsal/palmer) aspect of the hand in between the metacarpals.10. Gently pull the webs of fingers.11. Knead (rock and roll) by making a fist on the palmer aspect of patient’s hand, gently rotate using the knuckles to apply pressure 5 times.12. Caterpillar walk on all areas of the palm, working proximally (towards the body) (if patient is less comfortable with palm upwards continue with hand in a neutral position, palm down).13. Make small circles along the 5 zones of the palmer surface of the hand (proximal to distal).14. Targeting key reflex areas, PRESS AND RELEASE 2 times in each area:  a. Shoulder-neck ridge (base of fingers)  b. Solar plexus (center of palm, just below the knuckle), PRESS and SPREAD (diaphragm line—moving outwards in both directions) 5 times  c. Lateral aspect of palm  d. Medial aspect of palm  e. Pad of thumb14. Pinch lateral aspect of hand 3 times.15. Caterpillar walk on the medial border of thumb 3 times.16. Caterpillar walk on the fingers:  a. Caterpillar walk proximal making sure to cover all surface areas.  b. Rotate knuckles gently 3 times in each direction (proximal to distal).  c. Gently pull fingers.17. Finishing touches: SWEEP entire hand, HOLD, and switch to other side.18. Hygiene: Once both hands have been massaged, wash hands with cold water.

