### Data Analysis

The data will be entered in the SPSS software version 22.0 (IBM Corp), and a random subset of data will be used to identify missing or erroneous values. This study aims to use intention-to-treat analysis by including every participant who has been randomized, regardless of group assignment, study withdrawal, or protocol deviations.

Descriptive statistics will be calculated for sociodemographic and medical-surgical data and the baseline scores on all the outcome variables. Group differentiation in sociodemographic and medical-surgical characteristics for participant patients will be investigated using chi-square tests of independence for nominal level variables and one-way analyses of variance (ANOVA) for interval and ratio level variables. If group differences exist, the respective variable will be included as a covariate in the subsequent analyses. Frequencies and percentages of the location and descriptors of pain (ie, sensory dimension of pain) will be calculated for each group and assessment point and used to describe the pain characteristics of participants. Data on pain location and quality will be compared over time.

Repeated measures between ANOVA factors will be used to test for treatment (hand massage, hand-holding, rest), time (before, immediately after, and 30 minutes later), and interaction effect for pain intensity, pain unpleasantness, muscle tension, anxiety, and means of vital signs. This will be run for each intervention and each of these outcome variables. One ANOVA test will be performed for pain interference with the independent variable being group assignment (hand massage, hand-holding, standard care). The main comparison of interest is between the hand massage and standard care group and the difference in means pre- and immediately posttreatment.

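### The primary endpoint is stated inconsistently across four sections; session, time point and comparator need to be fixed once, and the power restated for that contrast

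*Protocol article*

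**What the plan says.** Four sections of the protocol article describe the primary question.

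- **Aim.** Massage is compared "versus hand-holding (ie, simple touch) and standard care on the postoperative pain intensity of adult ICU patients", so there are two comparators.
- **Sample Size and Sampling Procedure.** The trial is powered for a "difference in the pain intensity score of 1.5 between the hand massage and standard care group". The calculation is set "immediately after the third massage with a 2-sided significance level of .05", with SD 2.0, power .80, three equal arms and a repeated-measures design with three measurements. The minimum is 72 patients.
- **Primary Outcome.** The metric is the change in pain intensity from the pre-intervention reading "to immediately after each intervention and 30 minutes later". With three sessions, that makes six changes.
- **Data Analysis.** A repeated-measures ANOVA with three treatment levels and three times is specified, and "This will be run for each intervention and each of these outcome variables". The section then singles out one comparison: "The main comparison of interest is between the hand massage and standard care group and the difference in means pre- and immediately posttreatment". It does not say in which session.

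No section mentions an adjustment for multiple tests.

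**The concern.** A primary endpoint has to answer three questions before the data are seen: which session, which time point, which comparator. Here the answers differ by section, so more than one analysis could be presented as the primary one.

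The session matters clinically. The Background section reports that in the pilot trial a single massage gave no significant decrease in pain, while up to three massages looked promising. A positive result after session 1 and a positive result after session 3 would therefore support different conclusions. The article's Conclusion says the results should inform guidelines on the dose, timing and technique of massage.

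The comparator matters too. The Choice of Comparators section includes the touch arm to find out whether massage adds anything to touch. That question is in the primary aim, but the sample size is not built for it.

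**Working it through.** **1. The sections side by side**

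| Section | Session | Time point | Quantity | Comparator |
|---|---|---|---|---|
| Aim | all three | not stated | pain intensity | hand-holding and standard care |
| Sample Size | third | immediately after | score | standard care |
| Primary Outcome | each of three | immediately after and 30 minutes later | change | not stated |
| Data Analysis, main comparison | not stated (model run per session) | immediately after | pre-to-post difference | standard care |

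Sample Size and Data Analysis agree on time point and comparator. Only Sample Size names a deciding session. Primary Outcome is the furthest from the others.

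**2. The plan's figure of 72**

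Inputs from the document: difference 1.5, SD 2.0, two-sided .05, power .80, three arms, m = 3 measurements. Assumptions, because the document gives neither: arm means 0, 0.75 and 1.5, and correlation ρ = 0.5 between measurements.

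- Effect size f = SD(0, 0.75, 1.5) / 2.0 = 0.612 / 2.0 = 0.306.
- Noncentrality λ = N f² m / (1 + (m − 1)ρ) = 72 × 0.09375 × 3 / 2 = 10.1.
- Noncentral F with 2 and 69 degrees of freedom gives power 0.802, so N = 72 is reproduced.

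Means of 0, 0 and 1.5 with ρ = 0.8 also give 72. In either case the figure refers to a three-arm effect averaged over three measurements. It is not the power of one two-arm contrast at one time.

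**3. Power for the single contrast**

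With n = 24 per arm and d = 1.5 / 2.0 = 0.75, the noncentrality is 0.75 × √(24/2) = 2.60. A two-sample t-test (46 degrees of freedom, two-sided .05) has power 0.72. The normal approximation gives 0.74. Power of 80% by the t-test needs 29 per arm, or 3 × 29 = 87 in three equal arms.

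This takes SD 2.0 as the SD of the quantity analysed. If 2.0 is the SD of a single score, adjusting for the pre-session score multiplies it by √(1 − r²), where r is the pre-post correlation. Approximate power is then 0.76 at r = 0.3, 0.79 at r = 0.4 and 0.84 at r = 0.5. The document gives no r.

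**4. False-positive chance if any session may decide**

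For massage versus standard care, immediate change, three sessions each at .05, independence gives 1 − 0.95³ = 14.3%. Simulation under no effect, with 24 per arm, 40,000 trials and between-session correlation r (an assumption, since none is given):

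| r | at least one p < .05 |
|---|---|
| 0 | 14.6% |
| 0.3 | 13.6% |
| 0.5 | 12.6% |
| 0.7 | 10.8% |
| 0.9 | 8.4% |

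One named session gives 5%. Three per-session omnibus F tests of treatment give much the same range, 8.7% to 14.5%.

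**5. Wider readings**

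- Both controls, one session: about 9%.
- Both controls, three sessions: 15% to 25%.
- Massage versus standard care with the 30-minute changes added (six tests): 17% to 24%, for session correlations 0.3 to 0.7.
- The same with both controls (twelve tests): 29% to 40%.

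**The case against.** The strongest reply is that Sample Size and Data Analysis are compatible. Both single out massage versus standard care immediately after treatment, and Sample Size supplies the session missing from Data Analysis. Read together, they give one test at 5%. The .05 level appears only in the sample-size paragraph, and a fuller protocol or analysis plan that is not shown could set a multiplicity rule.

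Much of this stands. Inflation is possible, not certain, and the absence of adjustment is inferred from silence. But the benign reading has to set aside the section that formally defines the primary outcome, which includes all three sessions and the 30-minute reading. It also has to set aside the second comparator in the Aim. These are conflicts within the current text, and a later document would have to overrule part of it.

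A reader might infer a stronger claim: that the plan contains up to twelve primary tests, with an error rate near 40%. The documents do not support it. Data Analysis names one main comparison, and its three-arm model covers both controls and both post-treatment readings within each session. Twelve tests arise only by ignoring that sentence and testing every pair and time separately. The higher figures also need low correlation between sessions, although the same patients are measured three times within about a day.

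A reader might also infer that the hand-holding contrast has a known low power. The document gives no expected difference for that pair, so its power cannot be stated.

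**Conclusion.** The inconsistency is real and lies in the current text: the four sections do not agree on session, time point and comparator. The consequence is conditional. If a result in any session may carry the primary claim without adjustment, the false-positive chance for massage versus standard care is about 8% to 15%, for between-session correlations from 0.9 down to 0. It is higher if the 30-minute readings or the hand-holding contrast also count as primary. If the third session is the sole decider, it is 5%.

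A second consequence follows. The natural single contrast does not inherit the stated 80% power. At 24 per arm it has about 72% if SD 2.0 applies to the analysed quantity, before any gain from baseline adjustment.

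**What to change.** State one primary endpoint in Aim, Sample Size, Primary Outcome and Data Analysis: pain intensity on the NRS from before to immediately after the third session, hand massage versus standard care, two-sided .05. Say whether it is analysed as a change or as the post-session score adjusted for the pre-session score.

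Test massage versus hand-holding at the same time point second, in fixed sequence, only if the first test is significant. Make sessions 1 and 2 and all 30-minute readings secondary, reported as estimates with 95% confidence intervals. Reword the Aim to match this order.

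Restate the power for the named contrast, with the assumed SD and any assumed pre-post correlation given explicitly, and do not describe it as already powered at 80%.

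The cost is mainly wording, and no alpha has to be split. By comparison, keeping three sessions co-primary under Bonferroni would cut power at 24 per arm from 0.74 to 0.58 (normal approximation). A significant result in session 1 or 2 alone could no longer be claimed as primary, and the restated power may be somewhat less favourable. The Results section reports 24 patients already randomized, so the choice should be made before any comparison by arm.

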### Ethical Considerations

Ethical approval has been granted by the Research Ethics Committee of the study setting in February 2016. This protocol has been independently peer reviewed by McGill University and the Quebec Nursing Intervention Research Network, who funded the study (F242710).

Informed and written consent will be obtained from participants. The study’s aim and procedure, risks and benefits, right to refuse participation and withdraw at any time without any repercussions on the care provided, confidentiality of data, randomization process, and lack of financial incentives for participation in the study will be explained to patients. They will be equally informed that there is no guarantee that they will benefit from this study. While there are no known risks associated with hand massage and hand-holding, any harmful effects during these interventions will be noted and reported to the Research Ethics Committee.

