#### Passive Control Group

The passive control group will receive the standard care administered in the ICU including a 20-minute rest period including the environmental adjustments of the experimental and active control groups. The interventionist will be outside of the patient room and have no contact with the patient throughout the 20 minutes. The standard care includes the pharmacological and nonpharmacological treatments (eg, repositioning) used to promote recovery and pain relief. In the study ICU, cardiac surgery patients are automatically prescribed a pain management protocol that includes the regular administration of morphine and breakthrough doses of analgesia as needed.

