### Criteria for Modifying Interventions

The allocated interventions will be discontinued upon the participant’s withdrawal of consent or if skin irritation is suspected or patient comfort is disrupted due to the intervention itself, both of which will be reported as adverse events. Consenting participants will be retained in the trial whenever possible in spite of the discontinuation of the assigned intervention to allow remaining data collection and limit missing data.

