### Data Collection

Sociodemographic (eg, age, gender) and medical-surgical data (eg, type of cardiac surgery, analgesia) will be collected using standardized data collection sheets. Prior to the delivery of each intervention (hand massage or hand-holding) and before the first data collection for the standard care group, patients will complete a self-administered data collection sheet with 5 short questions using the NRS for the self-report of pain intensity, pain unpleasantness, and anxiety, a body map for identifying the site of pain, and an open-ended question for a description of the quality of pain. The interventionist will be masked to patients’ self-reports, which will be accessed only at the end of data collection to verify for missing data. The form will be completed before, immediately after the intervention (hand massage or hand-holding), and 30 minutes later, for a total of 3 data collection points per intervention. Those assigned to standard care will complete the form at similar times. This bundle of assessments will be repeated for each of the 3 interventions. Muscle tension and vital signs will also be evaluated at the same assessment points.

Finally, pain interference will be evaluated using a structured interview using the BPI on the second postoperative day to examine any carry-over effects.

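### Harm recording is unequal across arms as written: the rest arm has no equivalent record, and no common window runs past the last session

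*Protocol article*

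**What the plan says.** Two sections of the protocol article state what will be recorded as harm.

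- Ethical Considerations names hand massage and hand-holding and covers what happens while they are given: "hand massage and hand-holding, any harmful effects during these interventions will be noted and reported to the Research Ethics Committee".
- Criteria for Modifying Interventions says that allocated interventions are discontinued when a patient withdraws consent. It then gives the remaining grounds: "if skin irritation is suspected or patient comfort is disrupted due to the intervention itself, both of which will be reported as adverse events". It also keeps such patients under observation: "Consenting participants will be retained in the trial whenever possible in spite of the discontinuation of the assigned intervention".

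For the rest arm, Passive Control Group says: "The interventionist will be outside of the patient room and have no contact with the patient throughout the 20 minutes". Data Analysis makes hand massage versus standard care, meaning this arm, the main comparison.

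Outcome measurement is common to all arms. Data Collection says of the self-report sheet: "The form will be completed before, immediately after the intervention (hand massage or hand-holding), and 30 minutes later". For the rest arm it says: "Those assigned to standard care will complete the form at similar times". It then adds: "Muscle tension and vital signs will also be evaluated at the same assessment points". Table 1 has rows for pain, anxiety, muscle tension and vital signs, and none for harms or the skin of the hands. After the third session the only remaining entry is the pain interference interview on POD 2.

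**The concern.** The two harm rules differ in scope, and neither treats the arms alike. One covers any harmful effect, but only in the touch arms and only in session. The other has no session limit, but it counts disrupted comfort only when the intervention is judged to be the cause. An arm with no touch and no cream will produce little or nothing under either rule.

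The article says the results will inform practice guidelines and that massage could be introduced easily if effective. It also starts from the position that no risks are known. A low count gathered mainly in the touch arms would seem to confirm that position. A non-zero count could not be set against a background rate of the same events recorded in the same way in the rest arm.

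**Working it through.** The plan states no harm rate or harm-related sample size, so there is no figure of that kind to reproduce. The check is a comparison of the sections, followed by arm-size arithmetic.

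**Step 1. Scope of each rule**

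| Feature | Ethical Considerations | Criteria for Modifying Interventions |
|---|---|---|
| Events | Any harmful effect | Suspected skin irritation; disrupted comfort |
| Arms | Massage and hand-holding | Allocated interventions, no arm named |
| Window | During the intervention | Not limited to the session; no end stated |
| Attribution needed first | No | Yes for comfort: it must be due to the intervention |

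The rest arm falls outside the first rule. The second could reach it in principle, because Table 1 lists the rest period among the interventions. In practice, discomfort would have to be blamed on resting, and there is no cream to irritate the skin.

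**Step 2. Whether the common assessments fill the gap**

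The sheet asks for pain intensity, unpleasantness, anxiety, pain site on a body map and pain quality in the patient's own words. Hand pain or a worsening of symptoms could appear there in any arm. Three limits remain:

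- There is no item on the skin and no question about harm. Skin irritation is the one specific adverse event that the protocol names.
- The interventionist is masked to the sheets, which are opened only when data collection ends. An entry therefore cannot prompt a report at the time.
- The analysis treats these measures as efficacy outcomes, testing treatment, time and "interaction effect for pain intensity, pain unpleasantness, muscle tension, anxiety, and means of vital signs".

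The POD 2 interview uses the adapted Brief Pain Inventory. It asks about current pain, worst, least and average pain over 24 hours, and interference. It has no skin or harm item as described.

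Validity and Reliability describes a camera for checking the delivery of massage and hand-holding. Its stated purpose there is fidelity, and filming of the rest period is not mentioned.

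**Step 3. Size**

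- Patients per arm: 79 / 3 = 26.3, so about 26 patients, or one third, have no equivalent harm record.
- In-session time under the Ethical Considerations rule: 3 × 20 = 60 minutes per patient in each touch arm.
- Precision with complete capture and no events among 26 patients: one-sided 95% upper limit = 1 − 0.05^(1/26) = 0.109, or 10.9%. With 24 patients it is 11.7%, and with 27 it is 10.5%.

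The last figure depends only on arm size and is the same after the fix. It shows how little 26 patients can say about rare harms. It does not measure how many events the present wording would miss.

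**The case against.** The strongest reply is that this is a journal article and Ethical Considerations is a paragraph about reporting to the ethics committee. Adverse event forms, relatedness fields and detailed windows commonly sit in a full protocol that is not shown. No safety outcome appears among the objectives or outcomes, and no between-arm safety test is planned. That stands as far as missing detail goes: the absence of a harm row from Table 1 would not be a finding on its own. It does not answer the point that the article states two rules whose scopes differ from each other and fall unequally on the arms.

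A reader might also infer more than the text supports:

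- *That harms are recorded only in session and later events are missed.* Criteria for Modifying Interventions has no session limit, so irritation noticed between sessions could be reported. Every patient is also assessed 30 minutes after each session and interviewed on POD 2.
- *That the rest arm supplies no information on discomfort.* It completes the same ratings and has the same muscle tension and vital sign measurements. These give a control-arm picture of symptoms, though no adverse event record.
- *That the safety comparison is uninterpretable.* No such comparison is planned.
- *That the unmasked interventionist decides causality.* The text names no judge.
- *That the 60 minutes can be read as the share of follow-up observed.* This would need an assumed follow-up length and would ignore the second rule.

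**Conclusion.** The concern holds in a limited form. Followed as written, harm ascertainment is unequal across arms, the main comparator (about 26 of 79 patients) has no equivalent record, and no common window is set after the third session. The common assessments reduce the gap without closing it, because they carry no skin or harm item and the self-reports are not read in time.

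This is a minor to moderate point about unbiased harm reporting and patient safety. The primary outcome, its analysis and the sample size do not change. The number of events that would go unrecorded cannot be estimated from the document. The conclusion assumes that the full protocol, if it says more, does not already set one rule for all arms.

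**What to change.** Reconcile Ethical Considerations and Criteria for Modifying Interventions into one recording rule. Leave the grounds for discontinuing an intervention to the investigators.

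- **What:** the same listed items for everyone, namely hand skin reaction, disrupted comfort and any other harmful effect noted, recorded without first requiring attribution.
- **Who and when:** all three arms, at the existing assessments immediately and 30 minutes after each session, and at the POD 2 interview.
- **How:** add the row to Table 1, record relatedness in a separate field, and ask the harm items where the answer can be acted on, outside the sheets that stay closed until the end.
- **Reporting:** descriptive counts by arm, with no test.

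Logging every intensive care event whatever its nature would go further than needed.

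No new visit is required. The muscle tension assessment already involves moving the patient's upper limbs at these time points in every arm, so the hands can be looked at then. The cost is a few data-sheet items and some background events logged. At the time of the article 24 patients had been randomized, leaving 79 − 24 = 55 who could be covered. The report should say which patients were recorded under which rule.
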